#### Post-Stimulation Follow-Up Visits (Visits 21-24)

Visit 21 will take place within 1 week after Day 20 of treatment. The study team will aim to schedule the appointments as close as possible to the last FES study visit (Day 20). Subsequent visits will take place two, three, and four weeks after Day 20 of the intervention. Visits 21 to 23 will take place over videoconference and Visit 24 will happen on-site. Each follow-up visit will consist of the following:

- Psychiatric interview
  - Hamilton Depression Rating Scale 17-Item (HAM-D-17)
- Self-report scales using REDCap
  - 16-Item Quick Inventory of Depression Symptomatology (QIDS-SR-16)
  - Generalized Anxiety Disorder-7 Scale (GAD-7)
  - World Health Organization-5 Well-Being Index (WHO-5)
  - Pittsburgh Sleep Quality Index (PSQI)
- Assessment of CONMED record
- Assessment of FES Expectancy- will be completed with the subject using REDCap
- Review of FES side effects and adverse events

In the last follow-up visit (Visit 24) participants will return the stimulators and any unused electrode but they can keep the personalized masks. If participants do not complete the entire study, we may ask them to return to St. Michael's Hospital for some of the follow-up visits, including a psychiatric interview, self-report scales, and/or neuropsychological testing.

## 6.4. Clinical Scales and Self-Report Measures

All clinical assessments will be completed by a rater blinded to the treatment arm, or by participants themselves (self-report scales). On visits with both the clinical scales and treatment, the clinical scales will be completed after treatment. The rater will not be otherwise involved in the study. If the rater's blind is broken, it will be documented, and efforts will be made to find an substitute rater. All scales (both self-report and clinician-rated) will be administered using a tablet with a protected Microsoft® Access database for results to be safely and instantly loaded to the study database, with pen and paper versions available if there are technological difficulties.

- Montgomery Åsberg Depression Rating Scale (MADRS)

The clinician-administered MADRS will be used as part of the screening process. This is a 10-item clinician-rated scale designed to measure depression severity and detects changes due to treatment. Participants will need to obtain a minimal total score of 6 total at screening to be eligible for inclusion.

- Hamilton Depression Rating Scale 17-Item (HAM-D-17)

The 17-item Hamilton Depression Rating Scale (HAM-D-17) is a semi-structured, clinician-administered interview that has been well-validated in measuring the presence and severity of depression. This scale will be administered at baseline, at the end of each treatment week, and at each follow-up visit.

- 16-Item Quick Inventory of Depressive Symptomatology-Self Report (QIDS-SR-16)

The Quick Inventory of Depressive Symptomatology-Self Report (QIDS-SR-16) is a 16-item, self-rated survey that has been psychometrically validated to screen for depression, using the diagnostic criteria for MDD from the DSM-IV. This self-report measure will be done at baseline, during each treatment visit, and at each follow-up visit using REDCap.

- General Anxiety Disorder (GAD-7)

The GAD-7 is a 7-item self-rated questionnaire for assessing generalized anxiety disorder and its severity. Items are ranked on a 4-point scale from 0 (not at all sure) to 3 (nearly every day), providing a total severity score from 0 to 21. This self-report measure will be done at baseline, during treatment visits 5, 10, 15, and 20, and at each follow-up visit using REDCap.

- World Health Organization-5 Well-Being Index (WHO-5)

The WHO-5 Well-Being Index is a 5-item self-rated scale that is designed to measure well-being over the past two weeks. Participants will rate the frequency or consistency of each positive feeling on a 6-point scale from 0 (at no time) to 5 (all of the time). The sum of

scores from the five items will then be multiplied by 4, representing the participant's perceived quality of life as a percentage. This self-report measure will be done at baseline, during treatment visits 5, 10, 15, and 20, and at each follow-up visit using REDCap.

- Pittsburgh Sleep Quality Index (PSQI)

The PSQI is a self-rated scale containing 19 items that measure sleep habits and quality.

This scale is broken up into seven components that assess sleep quality, latency, duration, efficiency, disturbances, medication use, and daytime dysfunction. The sum of scores from all seven components will generate a global score of 0-21, with higher scores indicating lower sleep quality. This self-report measure will be done at baseline, during treatment visits 5, 10, 15, and 20, and at each follow-up visit using REDCap.

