#### Functional Electrical Stimulation Improves Symptoms of Major Depressive Disorder

Kapadia et al. (2019) conducted a follow-up open-label mixed-methods study on individuals with MDD, where they wanted to explore whether 10 sessions of the FES would lead to improvements in depressive symptoms. This study recruited 10 individuals with moderate-to-severe MDD, and all study participants received facial FES of the “Duchenne” muscles three times per week for a minimum of 10 sessions and a maximum of 40 sessions. All participants received 10 sessions of the FES and were invited to continue therapy for up to 40 sessions if they wished (5 out of 10 participants requested to undergo 40 FES sessions). The results were promising: participants experienced early improvements in depressive symptoms as measured by the Hamilton Depression Rating Scale (HAM-D) and Inventory of Depressive Symptomology (IDS) upon

completing 10 sessions of treatment. On average, the participants showed an improvement on the HAM-D by 8.1 points (SD = 5.26,  $p = .005$ ) and on the IDS by 14 points (SD = 11.05,  $p = .008$ ). Eighty percent of participants showed a reduction by at least 30%, 50% achieved clinical response (i.e., change in the HAM-D by at least 50%), and 60% entered remission. The reported adverse events were insignificant, involving commonly reported redness or skin irritation underneath the stimulation site, muscle soreness, and muscle discomfort. All participants enrolled in the trials adhered to the treatment protocol, showing high compliance. FES was well-tolerated, with the potential to be administered with limited physician oversight.

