## 5. Subject Selection and Recruitment

### 5.1. Inclusion and Exclusion Criteria

#### Inclusion Criteria

Patients will be included if they:

1. Meet the DSM-5 (67) criteria for unipolar MDD with a current MDE without psychotic features, with  $\leq 2$  failed treatment trials (non-treatment-resistant depression), as determined by a physician and validated by a MINI (68) done by a trained research assistant.
2. Have no change in the medication regimen or other forms of treatments (e.g., psychotherapy) for at least 4 weeks (28 days) prior to beginning the study, during the 20-session treatment period, and the 4-week post-treatment observation period. This will be established through self-report, in combination with the ATHF (69, 70) filled out by the participant.
3. Have an MDD diagnosis as confirmed by the MADRS (71) score of  $\geq 6$
4. Are above 18 years of age.

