### **8.2. Secondary Outcome Measures**

Secondary outcomes will include the A) change in depression symptoms, measured by the HAM-D-17 scale and the Quick Inventory of Depressive Symptomatology (QIDS-SR-16); B) change in anxiety, measured by the Generalized Anxiety Disorder-7 (GAD-7); C) change in quality of life, measured by the World Health Organization Quality of Life Questionnaire (WHO-5); D) change in subjective sleep, measured by the Pittsburgh Sleep Quality Index (PSQI); E) HAM-D-17 response and remission rates and sustainability of effects for up to 4 weeks (28 days) following the intervention. The choice of scales in this study has been informed by our pilot study; we have added the FES experience scale. The MADRS will be used for recruitment and the HAM-D-17 will be used for the evaluation of treatment response as per current best practice in clinical trials. Self-report questionnaires will be completed via REDCap.

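### Apart from a confirmed current episode, entry requires only a MADRS total of 6 and sets no minimum on the HAM-D-17, so some participants may have little room to improve or may count as remitters without changing

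*Protocol*

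**What the plan says.** Entry rests on two requirements that bear on severity.

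- Inclusion criterion 1 in section 5.1 is diagnostic: "Meet the DSM-5 (67) criteria for unipolar MDD with a current MDE without psychotic features", determined by a physician and validated by the MINI. It carries no score.
- Inclusion criterion 3 is numerical: "Have an MDD diagnosis as confirmed by the MADRS (71) score of" at least 6. Section 6.4 repeats it ("Participants will need to obtain a minimal total score of 6 total at screening to be eligible for inclusion"), and the trial summary gives the same value.

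Entry and outcome use different scales. Section 8.2 says: "The MADRS will be used for recruitment and the HAM-D-17 will be used for the evaluation of treatment response". The HAM-D-17 is named in Hypothesis 2, is the outcome of the ANCOVA in section 14.2, and defines a secondary outcome: "HAM-D-17 response and remission rates and sustainability of effects for up to 4 weeks (28 days) following the intervention". Table 1 marks it at screening (timepoint -3) and at Visit 0. The text of section 6.4 mentions only the later occasions: "This scale will be administered at baseline, at the end of each treatment week, and at each follow-up visit". No criterion anywhere uses a HAM-D-17 value, and no remission cutoff is given.

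The motivating evidence in section 3 comes from a more severe group: "This study recruited 10 individuals with moderate-to-severe MDD". Its mean HAM-D improvement was 8.1 points (SD 5.26).

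**The concern.** A MADRS total of 6 over 10 items is an average of 0.6 points per item. Someone who meets the episode criteria but scores low on the HAM-D-17 can therefore be randomised. Two consequences follow.

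1. **Limited room to fall.** A score cannot fall by more than its starting value. ANCOVA adjusts for baseline differences but cannot restore a reduction that a low baseline makes impossible.
2. **Remission by default.** If remission is an end score at or below a fixed value, a participant who starts there and stays there is counted as a success in whichever arm he or she is in. This pulls the two remission rates together.

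Section 14.2 wants preliminary effectiveness, the HAM-D-17 standard deviation and the baseline-to-follow-up correlation to plan a powered trial. All three depend on the severity mix that the entry rule lets in. The primary outcomes (feasibility, tolerability, safety) are not what is at stake here.

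**Working it through.** The plan gives no calculation behind the MADRS threshold or the sample size of 20, so there is no figure to reproduce. The threshold is the same (6) in the trial summary, section 5.1 and section 6.4.

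**Inputs from the protocol:** pilot HAM-D fall, mean 8.1 and SD 5.26; pilot remission 60%; 20 participants allocated 1:1, so 10 per arm.

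**Assumptions, not in the protocol:** pilot falls are roughly Normal; the share m of low-baseline participants is 10% to 50%; sham remission is 30% among the others; the low-baseline HAM-D-17 score is 7.

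**Step 1: attainable fall at baseline B.** Cap the fall D at B. With z = (B − 8.1)/5.26,

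E[min(D, B)] = 8.1·Φ(z) − 5.26·φ(z) + B·(1 − Φ(z)).

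For B = 7: z = −0.209, Φ = 0.417, φ = 0.390, giving 3.38 − 2.05 + 4.08 = 5.41.

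| Baseline HAM-D-17 | Share of pilot-type falls that would exceed it | Mean attainable fall |
|---|---|---|
| 4 | 78% | 3.4 |
| 6 | 66% | 4.8 |
| 7 | 58% | 5.4 |
| 8 | 51% | 6.0 |
| 10 | 36% | 6.8 |
| 14 | 13% | 7.8 |
| 20 | 1% | 8.1 |

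The loss is large at low baselines and negligible at high ones.

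**Step 2: effect on an arm's mean fall.** Mean = (1 − m)·8.1 + m·5.41.

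- m = 10%: 7.29 + 0.54 = 7.83 (3% lower)
- m = 20%: 6.48 + 1.08 = 7.56 (7% lower)
- m = 30%: 5.67 + 1.62 = 7.29 (10% lower)
- m = 50%: 4.05 + 2.71 = 6.76 (17% lower)

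**Step 3: effect on remission.** Let a share m of each arm be at or below the cutoff at baseline and remain there. Active rate = m + (1 − m)·0.60; sham rate = m + (1 − m)·0.30; difference = (1 − m)·0.30.

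| m (of 20) | Active | Sham | Difference | Odds ratio |
|---|---|---|---|---|
| 0 (0) | 0.60 | 0.30 | 0.30 | 3.5 |
| 10% (2) | 0.64 | 0.37 | 0.27 | 3.0 |
| 20% (4) | 0.68 | 0.44 | 0.24 | 2.7 |
| 30% (6) | 0.72 | 0.51 | 0.21 | 2.5 |
| 50% (10) | 0.80 | 0.65 | 0.15 | 2.2 |

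Step 3 does not depend on the cutoff chosen, only on its being an absolute end score.

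**Step 4: when a severity check could act.** Section 6.1 randomises once all baseline measures are collected. Table 1 marks allocation at timepoint -1, with mask delivery and before Visit 0. Under Table 1, a check at Visit 0 would come after allocation.

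**The case against.** The strongest reply is that a physician-determined, MINI-validated current episode is required, so very mild entrants should be uncommon. Broad entry is also defensible in a 20-person pilot whose primary outcomes include recruitment. This stands in part: it is why the shares above are assumptions and why no particular higher entry score is urged. It does not close the gap, because the diagnostic criterion sets no score. A definition of remission in a statistical analysis plan would not close it either, since eligibility is fixed in the protocol.

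Four stronger readings are tempting but unsupported.

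- **That the pilot already shows the problem.** Section 3 reports "50% achieved clinical response (i.e., change in the HAM-D by at least 50%), and 60% entered remission". A reader might infer that at least one pilot participant remitted without halving the score, and so started mild. The protocol gives neither scale nor timepoint for remission, and the pilot used both the HAM-D and the IDS. Even if the inference held, it would show remission without a 50% fall, not remission without improvement.
- **That Aims 2 and 3 cannot be answered.** Response is described there as a percentage fall, so a participant starting at 6 responds by falling 3. The contrasts are diluted only.
- **That severity lapses over a long gap between screening and Visit 0.** No interval is stated, and making the mask takes 10 to 15 hours. The HAM-D-17 is repeated at Visit 0; what is missing is a rule that uses it.
- **That the standard deviation and correlation will be biased in a known direction.** The protocol does not say whom the later trial would recruit. The figures will simply reflect the severity mix admitted here.

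**Conclusion.** The point holds as a design weakness in the secondary outcomes and is worth correcting, because the remedy uses a scale already scheduled. With 10% to 50% of participants entering at HAM-D-17 of 7, the attainable mean fall is about 3% to 17% lower. With the same shares at or below the remission cutoff, the assumed remission difference loses 10% to 50% of its size.

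These sizes rest on assumed shares, an assumed sham remission rate and an uncontrolled pre-to-post change from 10 people. The figures for the mean fall describe one arm's attainable change and do not estimate the loss in the between-arm HAM-D-17 difference. The actual number of low-baseline entrants cannot be derived from the protocol.

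**What to change.** 1. **Section 14.2:** compute remission only among analysed participants whose baseline HAM-D-17 is above the remission cutoff, and state the cutoff. Keep response, as a percentage fall, in all participants.
2. **Section 5.1:** require the HAM-D-17 that Table 1 schedules at screening, before mask fitting and allocation, to be above that same cutoff. Any higher floor is the sponsor's choice, to be weighed against recruitment. Add screening to the HAM-D-17 occasions listed in section 6.4 so that text and table agree. Item 1 is still needed, because a score can drop between screening and Visit 0.
3. **Section 6.1 and Table 1:** reconcile randomisation after baseline with allocation at timepoint -1, so that any severity check precedes randomisation and the baseline score defining the remission denominator is taken before allocation.

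Cost: wording changes, one added criterion on an assessment already scheduled, a few more screen failures and a slightly smaller remission denominator. Checking at screening avoids making masks for people who would then be excluded.

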## **REDCap**

Research Electronic Data Capture (REDCap; <https://www.project-redcap.org>) software supported by Applied Health Research Centre (AHRC) at UHT, will be used for data collection and overall study data management over the course of this project. REDCap is an open-source, web-based clinical data management and electronic data capture system and database. The system is developed and managed in compliance with UHT privacy, the Health Insurance Portability and Accountability Act, the Personal Information Protection and Electronic Documents Act, and Food and Drug Administration 21 Code of Federal Regulations Part 11 regulations, providing functions such as defined user roles and privileges, user authentication and encryption for in-transit data, de-identification of protected health information and comprehensive auditing features to record and monitor access and changes to data. This system will be used to send scheduled questionnaires to participants and store active data and data monitoring and for the query and export of datasets for statistical analysis and modeling.

Access to REDCap will be secured through a secure web portal and protected by multiple levels of authentication. A Project Coordinator will be assigned the project administrative privileges for study configuration, data collection management, and quality control.

Upon acceptance to the study, participants will complete mental health questionnaires on a daily and weekly basis. To complete these questionnaires, participants will receive an email notification with the REDCap survey link to their personal email address. Upon receiving the link, participants will answer the self-report questionnaires provided through the link. Active data will be sent to and stored on the REDCap server and will be linked by the unique ID for final analysis. Access to this data will only be granted to the project administrator to download the data from the REDCap server for analysis.

## **7. Trial Intervention**

The prepared mask and the stimulation system will be delivered to the users at the second on-site visit. The users will only need to place the mask on their faces and follow the instructions they

received at the mask delivery Visit. Half of the participants will self-deliver the treatments to follow the Duchenne pattern (active arm), the other half will self-deliver a non-Duchenne smile pattern (sham arm), the patterns will be pre-programmed into the take-home device.

### 7.1. FES Active (motor and sensory stimulation):

Participants allocated to the active arm will receive simultaneous transcutaneous FES therapy of bilateral zygomaticus major and orbicularis oculi muscles, which produce an expression of happiness according to the Facial Action Coding System^50. Surface self-adhesive electrodes will be placed bilaterally on the zygomaticus major and orbicularis oculi muscles (Figure 3). FES will be delivered simultaneously to all four muscle groups using the Twin Stim® Plus Digital TENS/EMS stimulator and the developed 3D mask. FES stimulation parameters to be used are 300µs long charge-balanced biphasic pulses delivered at 40 Hz, with amplitudes in the range of 1-25 mA to activate muscles, with alternating periods of stimulation and rest of 15 s duration each, these are stimulation values commonly used in FES studies for muscle activation (please refer to Figure 3 for electrode placement).

As done in the pilot study, participants will be reminded to attempt to voluntarily produce the desired expression (smile with the Duchenne marker) while being stimulated with the FES. Automated messages to voluntarily “smile & hold” (over speakers worn by the participant) precisely timed with the FES-related facial stimulations (only during 15 Sec ON times) will be delivered. Synchronized stimulation of four muscles (i.e., bilateral zygomaticus major and bilateral orbicularis oculi) will be delivered in a cycle consisting of 15 sec ON and 15 sec OFF, with “smile and hold” instructions automatically provided through speakers only during 15 sec ON time.

[figure not shown]

### 7.2. FES Sham (Sensory & non-patterned stimulation):

Participants recruited to the sham arm will also receive FES of the facial muscles in the same setup as the experimental group, but with only sensory stimulation (in the range of 1-8 mA stimulation – just enough to feel the stimulation, with other parameters the same as active arm) and in a non-Duchenne smile pattern.

Though we cannot be certain that this sham stimulation will be completely ineffective, the premise of the current trial is that facilitating the activation of “Duchenne muscles” via **patterned stimulation** will result in the reinforcement of neurological pathways responsible for mood elevation. This control group of **non-Duchenne pattern stimulation** will allow us to determine if the Duchenne Marker is key to improving patient outcomes. Further, this sham design is informed by guidelines for sham stimulation for neurostimulation studies.

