**Table 1: Study Schedule**

## 6.2. Randomization and Blinding

Participants will be randomized in a 1:1 allocation to receive FES (active pattern) or FES (sham pattern). Block randomization will be computer-generated, and the samples will be stratified for sex, given the potential differences in response and tolerability in these groups. A biostatistician will generate the randomization schedule, to be administered by a research assistant who is not associated with the study and instructed not to divulge group assignments to the participants to allow for concealment.

Participants and most study staff will be blinded. Only the physical therapist will need to monitor the participant. Measures taken to prevent functional unblinding include sensory and non-patterned sham and delivering automated messages to both active and sham groups. We will also evaluate each participant's ability to discriminate what treatment they received after each session to assess blinding effectiveness.

We will randomize subjects to study arms (20 days active or 20 days sham) using a secure online randomization module on REDCap. The block size will be fixed, and study personnel will be blinded to the randomization block size. An independent assistant, external to the study, will manage the randomization of subjects. The subject number and treatment code will be assigned

after the subject details have been obtained. Based on this information, the independent assistant will assign a unique subject number and treatment code, which will dictate the treatment assignment for the subject. The patterns will be pre-programmed into the take-home device by the biomedical team.

An unblinded code sheet that matches these stimulation codes to the treatment arm will be kept by an external coordinator and will not be available to the study coordinator or research assistants. The unblinded code sheet will have the following information:

1. The initial identifier codes for all potential participants
2. Stimulation code: 6-digit numerical code for the stimulation session
3. Condition number: Numerical code for the condition
4. Condition name: Name of the condition

A copy of this code sheet with the condition name removed will be provided to the study coordinator and research assistants. These linked codes ensure that the study coordinator and research assistants are kept blinded to the type of treatment each participant will receive.

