### FES Visits (20 Visits)

The FES study visits will be conducted at home with personalized masks and a programmable stimulator. Participants will be randomized to undergo either 20 days (weekdays) of FES once a day (20 visits) or 20 days of sham FES once a day (20 visits). Participants will be allowed to miss up to 2 treatment visits. Additional visits will be added on to reach the expected number of visits if it is within a reasonable timeframe as determined by the investigator.

The FES treatment sessions will be 60 minutes in duration (15 min for preparations and 45 min for the stimulation), delivered 5 times/week, for a total of 20 FES sessions. Each FES session will take place over a videoconference. The webcam will be used to record facial expressions during the study because the activation of particular muscles may later need to be confirmed and analyzed. The video recordings are mandatory, and participants' smiles will be detectable through the hollowed-out area around the eyes and the mouth, but only to be viewed by the study personnel for quality assurance purposes. Whenever the FES is on, participants will be required to voluntarily produce the Duchenne smile. Automated messages to voluntarily “smile & hold” (over speakers) precisely timed with the FES-related facial stimulations (only during 15 sec ON times) will be delivered.

Each visit (15 min preparations and 45 min stimulation) will consist of the following:

- A review of FES side effects and adverse events will be completed daily before and after stimulation.
- The users only need to place the mask on their faces and follow the instructions they received at the mask delivery Visit.
- 45 min of FES stimulation to target Duchenne muscles.
- Participant tolerance

- Subjects will be queried each day about their experience and how they are doing. If participants or their family members express that the participant is having difficulty, the study staff will work with them to reduce any possible burden.
- A participant “FES Experience” Assessment will be completed with the subject at the end of each week (Visits 5, 10, 15, and 20) via videoconference to monitor the participant burden.
- Psychiatric interview - will be completed with the subject at the end of each intervention week via videoconference appointment during the 20 days (sessions 5, 10, 15, 20).
  - Hamilton Depression Rating Scale 17-Item (HAM-D-17)

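### Section 7.2 says the sham control will settle whether the Duchenne marker is key, but the arms differ in stimulation level and pattern together, so the contrast cannot credit any effect to the pattern

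*Protocol*

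**What the plan says.** There are two arms. Section 6.2: "Participants will be randomized in a 1:1 allocation to receive FES (active pattern) or FES (sham pattern" being the alternative.

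- **Active arm.** Section 7 assigns it the Duchenne pattern. Section 7.1 describes stimulation of the zygomaticus major and orbicularis oculi on both sides, "with amplitudes in the range of 1-25 mA to activate muscles".
- **Sham arm.** Section 7 assigns it a non-Duchenne smile pattern. Section 7.2 says these participants "will also receive FES of the facial muscles in the same setup as the experimental group". The current is where that section departs from the active arm: it describes a regimen "with only sensory stimulation (in the range of 1-8 mA stimulation", set just high enough to be felt, with the remaining parameters as in the active arm.
- **Inference drawn.** Section 7.2 then says that this control group "will allow us to determine if the Duchenne Marker is key to improving patient outcomes".

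On voluntary smiling, the FES Visits part of Section 6.3 introduces both arms ("Participants will be randomized to undergo either 20 days (weekdays) of FES once a day (20 visits) or 20 days of sham FES") and then says, without naming an arm: "Whenever the FES is on, participants will be required to voluntarily produce the Duchenne smile". Section 6.2 lists, among the measures against unblinding, "delivering automated messages to both active and sham groups". Section 7.1 writes out the reminder to produce the Duchenne expression for the active arm. Section 7.2 says nothing on it.

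**The concern.** To show that the Duchenne marker matters, a trial needs arms that differ in the Duchenne pattern and are otherwise alike. Here the arms also differ in whether the current is meant to make muscles contract at all. If active FES does better, the cause could be the pattern, motor-level stimulation of facial muscles in any pattern, or the two together. If there is no difference, that does not show the pattern to be unimportant either.

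A second matter may weaken the contrast. Section 3 says that voluntarily making and holding an expression can itself bring on the emotion, more so when the person attends to muscles such as those of the Duchenne marker. If sham participants are also cued to make that smile, the sham arm carries a component that the protocol itself regards as possibly active.

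At stake is the reading of the results. Section 14.2 says the estimates will help to plan a larger efficacy trial. An attribution that the data cannot support could be carried into that trial's rationale.

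**Working it through.** The plan states no figure that depends on this point, so there is none to reproduce. The check is whether the design can identify the effect named in 7.2.

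**1. What varies between the arms**

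| Factor | Active | Sham | Source |
|---|---|---|---|
| Stimulation level | motor, 1-25 mA | sensory only, 1-8 mA | 7.1, 7.2 |
| Pattern | Duchenne | non-Duchenne | 7, 7.1, 7.2 |
| Voluntary Duchenne smile when FES is on | required | apparently required, not confirmed | 6.2, 6.3; 7.1 for active only; 7.2 silent |

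**2. The contrast.** Let μ be the sham mean, *a* the effect of motor rather than sensory level, *p* the effect of Duchenne rather than non-Duchenne pattern, and *i* their interaction.

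- Mean in active arm = μ + *a* + *p* + *i*
- Mean in sham arm = μ
- Active − sham = *a* + *p* + *i*

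Ignore the interaction and call the observed difference D. Then (*a*, *p*) = (D, 0), (0, D) and (D/2, D/2) predict exactly the same data. In the first the marker has no role; in the second it has the whole role.

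**3. Rank of the design.** Use columns for intercept, level and pattern, with 10 participants per arm (20 in total, 1:1). The active rows are (1, 1, 1) and the sham rows (1, 0, 0). The rank is 2 for 3 parameters. More participants only repeat the same two rows, so the rank stays at 2. The ANCOVA in Section 14.2 adjusts for baseline score and sex, which does not separate level from pattern.

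For comparison only, a layout that crossed level with pattern would have rank 3 for the same three columns. The missing cell that matters is motor-level stimulation in a non-Duchenne pattern.

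**4. Overlap of the ranges.** The sham range of 1-8 mA lies inside the active range of 1-25 mA. This does not rescue the inference. The stated purposes differ (muscle activation against sensation only), and amplitude within the active arm is not randomised.

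**5. Voluntary smile.** If it is required in both arms, its column is 1 throughout. The rank is then 2 for 4 columns, and the smile is aliased with the intercept. Its own effect cannot be estimated, but it does not bias active against sham. It changes what the contrast means: the effect over and above voluntary smiling, which may be smaller.

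**The case against.** The best defence is that 7.2 speaks of stimulation. Its premise is that patterned stimulation of the Duchenne muscles strengthens mood pathways, and evoked contraction of those muscles is how 7.1 produces the marker. On that view contraction is part of the marker, not a rival explanation. This is partly right. What remains is that the control removes contraction and pattern together, so the trial cannot tell Duchenne-patterned contraction from facial contraction in general.

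A second defence is that 7.2 concedes the sham may not be wholly inert. That caveat concerns whether the sham has any effect. It does not mention the joint change of level and pattern, and the claim follows it unqualified.

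A third is that little depends on the sentence, and this stands. The primary outcomes are feasibility, tolerability and safety. Hypotheses 1a to 3 do not mention the marker, and Section 14.2 reports FES against sham without using the attribution.

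A reader might go further and infer that both arms certainly perform the Duchenne smile, so that the arms share the very factor 7.2 claims to isolate. The documents do not support that. Sections 6.2 and 6.3 make cued smiling in sham the likelier reading. But 6.2 does not give the content of the sham messages, 7.1 states the reminder for the active arm only, and 7.2 is silent. Even if the smile is common to both arms, it is a co-intervention and not the stimulation pattern that 7.2 refers to. It may dilute the contrast, but it does not confound it.

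**Conclusion.** The claim in 7.2 is stronger than the design allows. The trial can estimate active FES against this sham as a package. It cannot attribute any difference to the Duchenne pattern, at any sample size. This rests only on the level and pattern assigned to each arm in Sections 7, 7.1 and 7.2, and it holds whatever sham participants are told about smiling.

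Possible dilution by voluntary smiling is a secondary, conditional point. It depends on reading 6.2 and 6.3 as applying to both arms, and the documents give no means of sizing it.

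A reader might also infer that the sham is invalid or the comparison uninformative. That does not follow: the package contrast is coherent and suits a feasibility trial. The practical effect is confined to one sentence of rationale and to any later interpretation that relies on it.

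**What to change.** 1. In Section 7.2, replace the sentence about the Duchenne marker with what the contrast estimates: the combined effect of motor-level, Duchenne-patterned FES against sensory-level, non-Duchenne FES. Delete the claim that the trial determines whether the marker is key.
2. Reconcile Sections 6.2, 6.3 (FES Visits), 7.1 and 7.2 on what sham participants are told to do while stimulation is on. If both arms are cued to smile, add that the contrast is over and above cued voluntary smiling. Do not add this until it is confirmed.
3. In the same edit, settle how the sham is described. The heading of 7.2 and the text of 6.2 call it non-patterned, while the body of 7.2 calls it a non-Duchenne pattern.

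No change to the arms, stimulation settings, sample size or analysis is proposed. The cost is a wording amendment and a narrower stated conclusion.
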